# Rumo zhentong Yin for blood-stasis-type osteoporotic pain: protocol of a randomized, single-blind, controlled trial

**DOI:** 10.3389/fragi.2026.1876169

**Published:** 2026-09-11

**Keywords:** blood-stasis syndrome, osteoporotic pain, randomized controlled trial, Rumo zhentong Yin, traditional Chinese medicine

## Abstract

**Background:**

Osteoporosis (OP) is a metabolic skeletal disease characterized by reduced bone mass and micro-architectural deterioration, with Osteoporotic pain (OPP) as its most common clinical symptom, which markedly impairs quality of life. Modern pharmacologic treatments’ limitations are obvious with population aging, so the cost-effective interventions for OPP are urgently needed. As an empirical formula, Rumo zhentong Yin has been created by the national renowned veteran Traditional Chinese Medicine (TCM) practitioner [name] for blood-stasis pain. Hence, this trial was designed to investigate the efficacy of Rumo zhentong Yin in treating blood-stasis-type OPP.

**Methods:**

A randomized, single-blind, controlled trial was designed to evaluate the efficacy of Rumo zhentong Yin combined with standard therapy for OPP. Eligible OPP patients were recruited and randomly assigned (1:1) to form either the control or treatment group. Both groups received standard treatment. The intervention lasted 3 months, with follow-up evaluations every 4 weeks. Primary outcome was pain scores; secondary outcomes included bone mineral density (BMD), bone-turnover markers, inflammatory cytokines, blood-stasis syndrome score and hematological indices.

**Anticipated Results:**

To our knowledge, this trial is the first clinical study of Rumo zhentong Yin for OPP, with the primary objective to provide robust clinical evidence supporting the integration of Traditional Chinese and Western medicine for OPP.

**Trial Registration:**

The trial was registered at the International Traditional Medicine Clinical Trial Registry (www.itmctr.ccebtcm.org.cn) on 2026-01-08 (ITMCTR2026000740).

## Introduction

As global aging accelerates, osteoporosis (OP) has become one of the emblematic disorders of the aging era. Characterized by continuous loss of bone mass and deterioration of bone micro-architecture, OP leads to increased skeletal fragility and a higher risk of fracture. Clinically, it presents as low-back pain, aching in the extremities, loss of height and, in many cases, fragility fractures (Chinese Medical Association Branch of Osteoporosis and Bone Mineral Diseases, 2022). More than 200 million people are affected globally, with women bearing the greatest burden (National Center for Chronic Noncommunicable Diseases, 2021).

Osteoporotic pain (OPP) is the chief complaint that brings patients to medical attention and the principal factor limiting their daily activities. About 85% of individuals with OP report pain (Dinges, 2026), comprising both acute fracture-related nociceptive pain and chronic persistent pain (Vellucci et al., 2018). This substantially compromises quality of life in elderly patients who frequently have multiple comorbidities and may precipitate anxiety, depression and other psychological problems (Lisowska et al., 2018).

Current pharmacologic management includes anti-osteoporotic agents and non-steroidal anti-inflammatory drugs (NSAIDs). These therapies, however, carry risks such as hypersensitivity reactions, fever, peptic ulceration and increased cardiovascular-thrombotic events. Traditional Chinese medicine (TCM) offers a safer and effective alternative. Herbal formulae not only relieve pain but also correct underlying constitutional imbalances, reduce dependence on analgesics, minimize adverse reactions and improve overall quality of life (Shima et al., 2016).

Blood stasis is not only a causative factor of osteoporotic pain (OPP) but also a pathological consequence of the condition itself. As a result, blood-stasis syndrome (BSS) represents one of the most commonly observed traditional Chinese medicine (TCM) patterns in patients with osteoporotic pain (OPP). Its cardinal manifestations include aching, weakness and stabbing pain localized in the lower back and knees—or throughout the body—together with limitation of movement. Applying the Practical Diagnostic Criteria for Blood-Stasis Syndrome (Table 1) markedly enhances the accuracy and reliability of BSS identification in clinical practice.

**TABLE 1 T1:** Schedule of trial.

Study phase Tests		Screening period (Day)	Treatment period (Day)		
Visit window		−3∼0	Day 30 of treatment	Day 60 of treatment	Day 90 of treatment
Basic history taking					
Informed-consent signature		×	​	​	​
Demographics		×	​	​	​
General data form		×	​	​	​
Medical and prior-treatment history		×	​	​	​
Inclusion/exclusion check		×	​	​	​
Randomisation and enrolment		×	​	​	​
Screening variables					
Bone-mineral density (BMD)		×	​	​	​
Treatment administration					
Test group		​	×	×	×
Control group		​	×	×	×
Efficacy end-points (assessment visits)					
BMD measurement		×	​	​	×
TCM syndrome score		×	×	×	×
Pain score (VAS)		×	×	×	×
Bone-turnover markers (β-CTX, PINP)		×	×	×	×
Inflammatory cytokines (TNF-α, IL-1)		×	×	×	×
Blood-stasis syndrome score		×	×	×	×
Blood-cell indices		×	×	×	×
Safety observations					
Height		×	​	​	×
Blood pressure		×	​	​	×
Electrocardiogram		×	​	​	×
Haematology		×	​	​	×
Liver function		×	×	×	×
Renal function		×	×	×	×
Coagulation profile		×	​	​	×
Adverse-event log		​	×	×	×
Other items					
Concomitant medication / therapy		×			
Study closeout	Withdrawals and drop-outs	×			
	Compliance and safety evaluation form	×			
	Abnormalfindings record	×			
	Studycompletion status	×			
Review & sign-off		×			

Rumo zhentong Yin—composed of Ruxiang (frankincense), Moyao (myrrh), Xuejie (dragon’s blood), Jiangxiang (dalbergia wood), Sumu (sappan wood), Gansong (nardostachys), Xixin (asarum), and Tubiechong (ground beetle)—is an empirical formula created by national TCM master [name] for blood-stasis pain. Although preclinical studies support the anti-inflammatory, analgesic, and bone-protective effects of its ingredients, robust clinical evidence is still lacking (Shima et al., 2016; Lisowska et al., 2018).

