### Outcomes

Primary endpoints: Pain score: Visual Analogue Scale (VAS); Mechanism indicators: 1.Bone-mineral density (BMD); 2.Bone-turnover markers: β-CTX and PINP; 3.Inflammatory cytokines: TNF-α and IL-1.

Secondary endpoints:1.Blood-stasis syndrome score; 2.Hematological indices: serum MCV, RDW-CV, MPV and PDW.

Safety endpoints:Height, blood pressure, 12-lead ECG, routine hematology, liver and renal function tests, and coagulation profile.

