### Sample size

This is a parallel, two-arm, superiority RCT. A pilot study (Tong-bi Bushen formula for osteoporosis with kidney-deficiency/blood-stasis pattern) showed mean ± SD VAS improvements of 2.45 ± 0.53 (combination) vs. 2.07 ± 0.53 (Western medicine alone). Using an independent-samples t-test in PASS 15.0.1 (α = 0.05 two-sided, power = 0.95, 1:1 ratio) gave 51 participants per arm; allowing 10% attrition, 114 participants (57 per arm) will be enrolled. Data collection and registration All data will be captured in a paper/e-CRF. Investigators will be trained in patient communication, CRF completion and all rating scales. After consent, baseline demographics, BMD, TCM syndrome score, VAS, bone-turnover markers (β-CTX, PINP), inflammatory cytokines (TNF-α, IL-1), blood-stasis score and haematological indices (MCV, RDW-CV, MPV, PDW) will be collected. Follow-up visits occur every 4 weeks for 3 months. Original data and biological samples will be retained for a minimum of 5 years following the conclusion of the study.

An independent Data Monitoring Committee (DMC) consisting of external clinical epidemiologists, data managers and biostatisticians with no conflicts of interest will review safety, CRF accuracy and participant confidentiality every 6 months and will advise on protocol modification or early termination if warranted.

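### Safety haematology has one on-treatment reading (day 90), although blood-cell indices that normally come from a blood count are also measured at days 30 and 60

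*Protocol article*

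**What the plan says.** Table 1 (Schedule of trial, printed with the Introduction) has four visit columns: screening, "Day 30 of treatment", and the corresponding visits at days 60 and 90. There is no column for an early-termination visit.

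- Under efficacy end-points, "Blood-cell indices" is marked at all four visits.
- Under safety observations, haematology is marked at screening and day 90 only.
- Also under safety, "Liver function" and renal function are marked at all four visits, and the "Adverse-event log" at days 30, 60 and 90.

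The Outcomes section keeps the two blood items apart. The secondary endpoint is "Hematological indices: serum MCV, RDW-CV, MPV and PDW". The safety list includes "12-lead ECG, routine hematology, liver and renal function tests, and coagulation profile". It gives neither the components of routine haematology nor its visit times, so Table 1 is the only place where the timing is fixed.

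The Statistical analysis section has one sentence on missing data. It prescribes LOCF and does not restrict it to efficacy variables.

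**The concern.** MCV and MPV are mean volumes of red cells and platelets, and RDW-CV and PDW describe the spread of those volumes. A laboratory ordinarily obtains all four from the automated count that also gives the routine haematology results. The trial therefore probably generates blood counts at days 30 and 60, but its schedule makes them part of the safety data only at day 90.

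This matters most for participants who do not reach day 90. The Withdrawal/discontinuation criteria include serious side-effects and adverse or allergic reactions, so some early leavers may be the people of most interest for safety. Participants also know their allocation (Randomisation and blinding), so leaving may differ between the arms. If LOCF is applied to safety laboratory values, an early leaver's day-90 haematology becomes the screening value, which records no change at all.

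**Working it through.** **Step 1. Marks in Table 1.**

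| Item | Screening | Day 30 | Day 60 | Day 90 | On-treatment visits |
|---|---|---|---|---|---|
| Blood-cell indices (efficacy) | yes | yes | yes | yes | 3 of 3 |
| Haematology (safety) | yes | no | no | yes | 1 of 3 |
| Liver and renal function (safety) | yes | yes | yes | yes | 3 of 3 |

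Two visits, days 30 and 60, have blood-cell indices but no safety haematology.

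**Step 2. How many participants could lack a day-90 value.** The Sample size section gives 51 per arm before attrition, 10% attrition, and 57 per arm (114 in total) after it. This reproduces: 51 / (1 − 0.10) = 56.7, rounded up to 57, and 2 × 57 = 114.

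- 10% of 114 = 11.4.
- Enrolled minus required completers: 114 − 2 × 51 = 12.
- The Study design and setting section instead gives a total of 100. On that figure, 10% of 100 = 10.

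The range is about 10 to 12. It is an upper figure for this purpose, for two reasons:

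- Participants who leave before day 30 have no on-treatment sample under either schedule.
- The Drop-out criteria also count late attendance and poor adherence, and such participants may still give a day-90 sample.

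The documents give no timing of drop-out, so the number who would gain cannot be calculated.

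**Step 3. What LOCF would do if applied to safety haematology.** The only earlier safety value is the one at screening, so the imputed change is screening − screening = 0. Suppose 6 of 57 in an arm (57 − 51) were filled this way, and assume their true mean change equalled that of the 51 completers. The arm's mean change would then be multiplied by 51/57 = 0.895, a shrinkage of about 11% towards zero. If the leavers had larger changes than the completers, the loss would be greater. This is an illustration at the upper figure, not an estimate.

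**The case against.** The strongest reply is that nothing here is contradictory. The article defines two items and gives each its own schedule, and how often to schedule safety haematology is a design judgement. That stands: a reader might infer an internal contradiction, and there is none.

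A reader might also infer that two of the three on-treatment safety readings are thrown away. The documents do not support that either:

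- The day-30 and day-60 values are scheduled as a secondary efficacy endpoint, not as safety readings.
- No section says they will be kept out of safety review.
- The article does not state that haemoglobin, white-cell or platelet counts are recorded at those visits. That a full count lies behind the indices is usual laboratory practice and an assumption here.

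Nor is safety unobserved in between. Adverse events, liver function and renal function are covered at days 30 and 60, Table 1 lists a record of abnormal findings, and a data monitoring committee reviews safety every 6 months. A reaction that led to withdrawal should appear in the adverse-event log. The LOCF sentence is general, and a full protocol or SAP that is not shown may confine it to efficacy.

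These points narrow the concern but do not remove it. The printed schedule fixes a single on-treatment safety haematology reading, while the same test is in all likelihood being run at two further visits.

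**Conclusion.** The point holds as a small improvement to the design. As scheduled, safety haematology depends on one on-treatment visit, and a participant who leaves before it contributes none. If LOCF is applied as written, that participant contributes a change of zero. At most about 10 to 12 participants are concerned at the planned attrition, and the number who would gain from a change is smaller and unknown. For everyone else, the gain is two further on-treatment readings.

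The conclusion rests on two assumptions: that the indices at days 30 and 60 come from a full blood count, and that the LOCF rule covers safety laboratory values. It does not show that data are being discarded or that safety is unmonitored between screening and day 90. The sample size, error rate and primary analysis are not affected.

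**What to change.** Confirm with the laboratory that the day-30 and day-60 indices come from a full blood count. Where they do:

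1. Enter those counts in the safety section of the CRF.
2. Mark days 30 and 60 in the safety haematology row of Table 1.
3. Summarise observed haematology values by visit and arm in the safety analysis, so that no screening value stands in for a missing on-treatment one.

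The cost is a few more CRF fields at two visits and a few more rows in the safety tables. No new blood draw is needed and no clinical rule changes.

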## Methods and analysis

### Study design and setting

The protocol was approved by the Medical Ethics Committee of Xi’an Hospital Affiliated to Shaanxi University of Chinese Medicine (approval No. LLSCYJ2025085) and registered at the International Traditional Medicine Clinical Trial Registry (ITMCTR2026000740). The experimental flowchart is shown in Figure 1.

**FIGURE 1 F1:**
[figure not shown]
Trial flow chart.

This is a single-centre, two-arm, single-blind, randomized controlled trial. A total of 100 participants will be recruited through advertisements and referrals by outpatient and inpatient clinicians. Eligible patients will be informed about the study when they attend the outpatient clinic or are admitted to the hospital. A detailed face-to-face interview will be conducted to explain the study’s purpose, interventions, assessment procedures, and follow-up schedule. Following the provision of written informed consent, participants will be randomly assigned (1:1) to either the treatment group or control group. Both groups will receive standard care throughout the intervention period. In addition, the treatment group will receive Rumo zhentong Yin decoction, while the control group will receive standard care alone. The intervention will continue for up to 3 months, unless a participant withdraws consent, is lost to follow-up, or dies. Follow-up visits will be scheduled every 4 weeks, as outlined in Table 1.

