### Randomisation and blinding

Simple randomisation was used. The allocation sequence was generated using SPSS version 24.0. Each unique allocation code was placed in a sequentially numbered, opaque, sealed envelope (numbered 1–114) and stored by an independent custodian. After obtaining informed consent, the next envelope in sequence was opened, and the participant was assigned to either the control or treatment group (n = 57 per group). Because the two interventions could not be blinded to participants, only the outcome assessors, data managers, and statisticians were masked to group assignment. In the Case Report Form (CRF), group labels were replaced with the identifiers“A” and “B.” The master randomisation list (containing the sealed code linking A/B to actual groups) was generated by an external statistician using SAS software and is securely stored by the study administrator. It will remain concealed until after final database lock.

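### The protocol gives two enrolment targets, 100 and 114; only 114 agrees with its own sample-size calculation, and 100 gives about 92% power, not 95%, after the planned attrition

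*Protocol article*

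**What the plan says.** The protocol article states the planned size in three places.

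- **Study design and setting** (the paragraph after the flow chart): "A total of 100 participants will be recruited through advertisements and referrals by outpatient and inpatient clinicians". The same paragraph goes on to consent and 1:1 randomisation of these participants, so the number refers to people entering the trial.
- **Sample size**: the calculation "gave 51 participants per arm; allowing 10% attrition, 114 participants (57 per arm) will be enrolled". Its inputs are "mean ± SD VAS improvements of 2.45 ± 0.53 (combination) vs. 2.07 ± 0.53 (Western medicine alone" and "α = 0.05 two-sided, power = 0.95, 1:1 ratio", with an independent-samples t-test.
- **Randomisation and blinding**: each code goes into a "sequentially numbered, opaque, sealed envelope (numbered 1–114"), and the participant is then "assigned to either the control or treatment group (n = 57 per group").

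Two sections therefore agree on 114, and one says 100.

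**The concern.** The planned sample size should have one value. It tells the team when recruitment is complete, it supports the power claim, and it is the figure against which the final report compares achieved enrolment. With two values, a trial that closes at 100 could be described either as fully recruited or as 14 short of 114 (14/114 = 12%).

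The two values also do different things. The 114 is built to leave 51 per arm after attrition. The 100 has no derivation. If it governs, the 95% power in the Sample size section is not delivered, and the 57 per group in the Randomisation and blinding section cannot be reached, because envelopes 101 to 114 would never be opened.

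The Trial status section shows enrolment under way and due to close on 31 December 2026, so the target needs settling while recruitment is still open.

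**Working it through.** **Inputs** (all from the Sample size section)

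- Difference in mean VAS improvement: 2.45 − 2.07 = 0.38
- Common SD: 0.53, so the standardised difference is 0.38/0.53 = 0.717
- Two-sided α = 0.05 (z = 1.960); power 0.95 (z = 1.645); allocation 1:1
- Attrition: 10%

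**Step 1. Reproduce the plan's figure.**

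n per arm = 2 × (1.960 + 1.645)² × (0.53/0.38)² = 50.56, rounded up to **51**.

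Inflation: 51/(1 − 0.10) = 56.7, rounded up to **57 per arm, 114 in total**.

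Both stated figures reproduce. (The exact noncentral-t calculation needs 52 per arm, hence 52/0.9 = 57.8, i.e. 58 per arm and 116 in total. That is the ordinary gap between the two methods and is not counted as an error.)

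**Step 2. Look for a reading that reconciles 100 with 114.**

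- Evaluable total: 2 × 51 = 102, not 100.
- 114 less 10%: 114 × 0.9 = 102.6, not 100.
- Recruited versus enrolled: the number recruited cannot be smaller than the number enrolled.
- A superseded or interim figure: the article does not label it as either.

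None works.

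**Step 3. Patients left if 100 are enrolled.**

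100 × 0.9 = 90, so 45 per arm, against 102 (51 per arm) required.

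**Step 4. Power at each size.**

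Normal approximation: power ≈ Φ(0.717 × √(n/2) − 1.960). For n = 45, 0.717 × √22.5 = 3.401, and Φ(3.401 − 1.960) = Φ(1.441) = 0.925. The noncentral-t column uses the same noncentrality with 2n − 2 degrees of freedom.

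| Enrolled | Attrition | Per arm analysed | Power, noncentral t | Power, normal |
|---|---|---|---|---|
| 114 | none | 57 | 96.7% | 96.9% |
| 114 | 10% | 51 | 94.8% | 95.2% |
| 100 | none | 50 | 94.4% | 94.8% |
| 100 | 10% | 45 | 92.0% | 92.5% |

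By the noncentral t, moving from 51 to 45 per arm raises the type II error from 5.2% to 8.0%. By the normal approximation it rises from 4.8% to 7.5%.

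**The case against.** The strongest reply is that the operative target is easy to identify. The two sections that work with the number agree on 114, while the 100 appears once, without derivation, in a sentence about recruitment routes. It is probably a leftover. Even if it were the real target, about 92% power is good by usual standards. That is all fair, and it bears on how serious the point is. It does not remove the contradiction.

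Three further points deserve weight.

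- **Method of calculation.** The plan's 51 per arm reaches 95% by the normal approximation but gives 94.8% by the noncentral t. The shortfall at 100 with no attrition (94.4% against 94.8%) is therefore trivial in power terms; it matters only as a breach of the plan's own stated requirement. The loss that counts is the one after attrition, and it is 2.7 to 2.8 points on either method when compared with 51 per arm.
- **LOCF.** The Statistical analysis section imputes missing values by last observation carried forward, so some drop-outs may stay in the analysis. The analysed number would then lie between 45 and 50 per arm, and 45 is the lower end under the plan's own attrition rate. Carrying values forward may also dilute the effect, so this does not show that power would be higher.
- **Choice of stopping point.** Participants are not masked, but outcome assessors, data managers and statisticians are, and the group code stays concealed until after database lock. The article describes no unblinded efficacy look. A choice between 100 and 114 driven by results is therefore not something the documents suggest. The ambiguity is a problem of definition and reporting.

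**Conclusion.** The concern holds. The article states 100 in one place and 114 in two, and no reading reconciles them. The 114 follows correctly from the stated inputs, so this is an inconsistency between sections; the sample-size arithmetic itself is sound.

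If 100 governs, the plan's 10% attrition leaves 45 per arm instead of 51 and power of 92.0% to 92.5% instead of 95%. The trial would still be well powered on its own assumptions. What must be corrected is an unfixed planned size and a power statement that is wrong for one of the two sizes given.

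These figures take the plan's difference of 0.38 and SD of 0.53 as given, assume equal arms, and remove drop-outs from the analysis as the inflation step implies. The numbers in the registry entry and the ethics approval were not available, nor was the flow chart, so which target was approved cannot be determined here.

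**What to change.** Check which total the ethics committee approved and the registry holds, then use that one number throughout.

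- **If 114:** change the total in Study design and setting from 100 to 114 (57 per arm). Nothing else on this point needs to change.
- **If 100:** rewrite the Sample size section as 50 randomised and 45 evaluable per arm with about 92% power, and in Randomisation and blinding change the envelope range to 1–100 and the group size to 50.

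In either case confirm that the flow chart shows the same total. The first option costs one number in one sentence. The second costs a slightly less favourable power statement and edits in two sections. Any mismatch with the registry or the ethics approval would need an amendment, best made while recruitment is open.
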